#### Data analysis

The continuous variables will be summarized as mean ± standard deviation (SD) and the categorical variables will be described in frequency and percent. The baseline characteristics will be compared by either the Student t-test for the continuous variables or χ^2^-test for the categorical data. All analyses will initially be done on an intention-to-treat basis (ITT) and all participants will be included in the analyses if the relevant outcome variables have been collected. A per-protocol analysis will also be conducted for the primary and secondary outcome if there are a considerable number of protocol violators. For the primary outcome, a one-way ANCOVA will be used comparing differences in post-intervention UIC between the intervention group and the control group with the pre-intervention UIC as a covariate, as it is believed that the post-intervention UIC will depend, to some degree, on the pre-intervention UIC. For the secondary outcome, we will use linear regression to compare the mean Bayley-III cognitive score, the language scores (receptive and expressive separately and as a composite score) and the motor scores (fine and gross motor separately and as a composite score) between the two groups. The Bayley-III scores will be used on a continuous scale and is expected to be normally distributed. We will also investigate potential effect modification by other nutrients and confounding factors. In the case of unanticipated differences occurring between the intervention and control group, we will adjust for that/those factor(s) in the analyses for both the primary and secondary outcome. For the other outcomes, we will use a variety of statistical approaches where the data may be used as predictors, mediators or moderators. These analyses will be based on plans of analyses for the specific research questions that are addressed. Multilevel linear modeling will be applied to assess longitudinally data. Statistically significance will be set at *p* < 0.05.

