### Trial design

The study is a two-armed randomized controlled intervention trial involving cod intake in pregnancy with the primary purpose of prevention. The ideal control would be pregnant women from the same trial whom were to be instructed to continue with their habitual diet with restriction to include iodine. For ethical reasons the control is pregnant women, within the same trial, who will continue with their habitual diet. The primary outcome is UIC measured at post intervention (gestational week 36), and the secondary outcome is neurodevelopment assessed by the cognitive, language and motor scales of the Bayley Scales of Infant and Toddler Developmental 3rd edition (Bayley-III) when the infants are 11 months of age. Other outcomes include urine samples, dietary data and blood samples from the mother and from the infant, as well as data on child development such as developmental status, socio-emotional abilities and infant sleep, and maternal mental health, that will be collected at several time points during the first year of life.

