### Dietary intervention

#### Study foods and instructions

Participants in the intervention group will receive frozen cod fillets (Lerøy A/S, Bergen, Norway) and are asked to consume two intervention meals of 200 g weekly (a total of 400 g cod per week). They will prepare the dinner meal themselves and are free to choose recipes. However, they will be provided with recipes that could be used ad libitum. For compliance purposes, participants will be instructed to weigh (Kitchen Scale, article no. 34–1207-16, ClasOhlson.com) the cod fillet before preparing the meal, and weigh the fillet leftovers (if any), after the meal is completed. The participants will record these data, in addition to receipt used and date of consumption, in a weight registration form. These data will be used in order to calculate iodine intake from the intervention meal. The participants in the control group will be instructed to follow their habitual diet. Once a pregnant woman is enrolled or randomized, the study investigators will make every reasonable effort to follow the participant for the entire study period. Prior to all the visits, the participants will be reminded about the upcoming appointment. Study investigators will always take into account the participants’ private calendar in the attempt to best ensure retention.

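### The conditional per-protocol analysis is likely to exclude women mainly from the cod arm, and this supplementary comparison is biased if adherence is related to outcome

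*Protocol article*

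**What the plan says.** **Order of analyses.** The Data analysis section of the protocol article starts from ITT: "All analyses will initially be done on an intention-to-treat basis (ITT) and all participants will be included in the analyses if the relevant outcome variables" are available. It then adds: "A per-protocol analysis will also be conducted for the primary and secondary outcome if there are a considerable number of protocol violators". The primary outcome, urinary iodine concentration (UIC) at gestational week 36, is analysed by ANCOVA with baseline UIC as covariate. For infant development the text reads "For the secondary outcome, we will use linear regression to compare the mean Bayley-III cognitive score", followed by the language and motor scores; no baseline covariate is named. The section also provides for adjusting both outcomes if group differences appear that were not expected.

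**What each arm can comply with.** Under Study foods and instructions, women in the cod arm "are asked to consume two intervention meals of 200 g weekly (a total of 400 g cod per week"). The same section continues "For compliance purposes, participants will be instructed to weigh" the fillet before cooking and to "weigh the fillet leftovers (if any), after the meal is completed", and these weights go on a registration form. For the other arm it says: "The participants in the control group will be instructed to follow their habitual diet". Under Trial design the absence of an iodine restriction is deliberate: "For ethical reasons the control is pregnant women, within the same trial, who will continue with their habitual diet".

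**The concern.** A per-protocol set is built by removing women who did not follow their assignment. Here one arm has a weekly amount to eat and a form that records it. The other is asked only to carry on as before, and a control who habitually eats cod breaks no rule. The exclusions will then tend to come from one side.

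The mothers are not blinded, so keeping up two cod meals a week for 16 weeks is partly a matter of choice. Women who persist may differ from those who stop in ways that bear on UIC or infant development, such as liking for fish, education, nausea or mental health. If the low adherers leave the cod arm while their counterparts stay among the controls, the groups are no longer those that randomisation made. A difference on Bayley-III could be read as a benefit of cod when it reflects who kept eating it.

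The condition for running the analysis is a separate and smaller weakness. It does not cause the asymmetry. But for a given difference between compliers and non-compliers the bias grows with the share excluded, so the plan calls for this analysis in the circumstances where the bias would be largest.

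**Working it through.** The plan gives no figure for the per-protocol analysis, so there is none to reproduce. The check asks how large the distortion could be.

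**Inputs**
- From the document: 60 women per arm (Sample size calculation) and significance at p < 0.05 (Data analysis), taken as two-sided.
- Assumed, because the document gives neither: the share q of the cod arm excluded, and the difference d (in outcome SDs) that compliers and non-compliers would show without any cod effect.
- Also assumed: true effect zero, no exclusions among controls, outcome SD of 1 in both groups, and 15 points as the SD of a Bayley-III composite score.

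**Bias.** By randomisation the control arm holds the same mixture as the cod arm did before exclusions:

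control mean = (1 − q) × complier mean + q × non-complier mean

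The per-protocol cod arm has the complier mean. Subtracting, bias = q × d.

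**False-positive rate.** The test statistic is shifted by q × d / √(1/(60(1 − q)) + 1/60), and the two-sided rejection probability at ±1.96 follows from the normal distribution.

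| q | d (SD) | Bias (SD) | Bias (points) | Standard error (SD) | Shift | False-positive rate |
|---|---|---|---|---|---|---|
| 25% | 0.3 | 0.075 | 1.1 | √(1/45 + 1/60) = 0.197 | 0.38 | 6.7% |
| 25% | 0.5 | 0.125 | 1.9 | 0.197 | 0.63 | 9.7% |
| 40% | 0.3 | 0.120 | 1.8 | √(1/36 + 1/60) = 0.211 | 0.57 | 8.8% |
| 40% | 0.5 | 0.200 | 3.0 | 0.211 | 0.95 | 15.8% |

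**Check under a different selection model.** In 20,000 simulated trials per scenario (60 per arm, no true effect), the least compliant fraction f was removed from the cod arm only, with an assumed correlation r between compliance and outcome.

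| f | r = 0 | r = 0.2 | r = 0.3 | r = 0.5 |
|---|---|---|---|---|
| 10% | 5.1% | 5.3% | 6.7% | 8.3% |
| 20% | 5.1% | 6.6% | 8.4% | 15.0% |
| 30% | 5.0% | 7.8% | 11.3% | 24.0% |
| 40% | 4.8% | 8.8% | 15.1% | 33.8% |

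With r = 0 nothing happens. With no exclusions, as under ITT, the rate stays near 5%. With the same selection applied to both arms (f = 30%, r = 0.5) the bias is 0.00 SD and the rate 5.9%. The bias therefore comes from one-sided exclusion together with a link between adherence and outcome.

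**Which outcome is more exposed.** For UIC, the baseline covariate removes part of any selection. For Bayley-III no prespecified covariate does. The Data analysis section lists seven Bayley-III scores (cognitive; language composite, receptive and expressive; motor composite, fine and gross), and the rates above apply to each.

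**The case against.** **The per-protocol set is undefined.** A reader might infer that the plan compares selected cod eaters with every control. The text does not say so. Controls have an instruction, and a marked change of diet would depart from it. The food frequency questionnaire is completed by both groups in gestational weeks 18 and 35, the food diary is repeated, and the six-day urine collection applies to both arms. Eligibility breaches could also count as violations in either arm. This stands: the asymmetry is likely, not stated. Even so, the document gives none of these instruments a compliance role, whereas it does give one to the weighing form.

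**Definitions belong in an analysis plan.** The criteria for a violator and the threshold for the trigger are ordinary content of an analysis plan, which is not shown. Their absence from the article is not a fault. Violators could also be counted without looking at UIC or Bayley-III.

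**ITT is protected.** It comes first and the per-protocol analysis is additional. One might read the word initially as leaving open which analysis decides, but nothing in the text lets per-protocol replace ITT, and that reading is strained.

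**Bayley-III is not wholly unadjusted.** The section allows adjustment for unexpected group differences. That is true, but such adjustment is post hoc and cannot reach unmeasured reasons for adherence.

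**The size is assumed.** The document gives neither q nor d, and even the sign of d is unknown, so the bias could run in either direction.

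**Conclusion.** The point holds for the supplementary per-protocol comparison only. The regimen and compliance record described in the article make exclusions likely to fall mainly on the cod arm. If adherence is related to outcome, the comparison is then biased by about 0.08–0.20 SD, with a false-positive rate of about 7–16% per score. This assumes 60 per arm, 25–40% of the cod arm excluded, a 0.3–0.5 SD complier difference and no exclusions among controls. If adherence is unrelated to outcome, or selection is the same in both arms, there is no bias. Bayley-III is more exposed than UIC.

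The documents do not support the stronger conclusion that the trial's main result is at risk, because the ITT comparison remains randomised. Nor do they show that all controls are kept in the per-protocol set. The change is still worth making, because data the trial already collects allow an adherence estimate without this selection.

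**What to change.** 1. State that ITT decides the conclusion for both the primary and the secondary outcome.
2. Replace the conditional per-protocol analysis with one adherence analysis, run whatever the number of violators. Keep all randomised women with the outcome and use allocation as the instrument. Take as exposure the weighed study cod eaten as a fraction of the assigned amount, with controls at 0 because they receive no study cod, and use the same covariates as the ITT model. The estimate is in essence the ITT effect divided by mean adherence in the cod arm.
3. If a per-protocol set is still shown, define violators for both arms in advance and label it supportive.

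**Cost.** Wording, and one further model on forms already being collected. The interval widens. If adherence were all or nothing with 25% not adhering, the standard error would be √(2/60)/0.75 = 0.183/0.75 = 0.243 SD, against 0.197 for per-protocol, or about 23% wider. With 40% not adhering it would be 0.183/0.60 = 0.304 against 0.211, or about 44% wider.

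The exposure rests on self-recorded weights, which may be missing in poor compliers. The method also assumes that allocation acts only through the study cod eaten, which is open to doubt if study cod displaces other fish. The test is essentially the ITT test, so the gain is not power but an adherence-adjusted estimate free of the selection described above.

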### Statistical considerations

#### Sample size calculation

A sample size of 60 women/group will have a 95% power to detect a 30% higher UIC in the intervention group compared to the control group (i.e., median UIC of ~120 μg/L compared with 80 μg/L. A total sample size of 144, divided into two groups, is anticipated, taken into account a 20% drop out rate. Data from the “Little in Norway” cohort has been applied in the power calculation of sample size. The following simplified equation has been used to calculate daily iodine intake and UIC [28]: *UIC / 0.92 x (0.0009 L/h/kg × 24 h/d) x weight (kg) = daily iodine intake.* The median UIC was 82 μg/L and the estimated iodine intake was 114 μg/day. The intervention group in this study will be given 400 g of cod per week, with an approximate iodine content of 100 μg/100 g. This intake will increase the mean estimated intake of iodine per week from 800 μg to 1200 μg.

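### The primary effect is planned as a relative difference in median UIC, but the primary ANCOVA as worded estimates a difference in mean UIC in μg/L; the scale should be fixed before unblinded analysis, with log UIC as the natural choice

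*Protocol article*

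**What the plan says.** **Planning (Sample size calculation).** The trial claims "95% power to detect a 30% higher UIC in the intervention group compared to the control group" and illustrates this with a "median UIC of ~120 μg/L compared with 80 μg/L". The reference cohort is also described by its median: "The median UIC was 82" μg/L. The supporting intake argument is put differently, as a mean and a fixed weekly addition: "This intake will increase the mean estimated intake of iodine per week from 800 μg to 1200 μg". No SD, coefficient of variation (CV), interquartile range or distributional shape is given for UIC, and neither the test nor the scale behind the power figure is stated.

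**Analysis (Data analysis).** The primary model is described thus: "a one-way ANCOVA will be used comparing differences in post-intervention UIC between the intervention group and the control group". Baseline is adjusted for on the same terms, the model being fitted "with the pre-intervention UIC as a covariate". No transformation is named for outcome or covariate. The general descriptive rule is "The continuous variables will be summarized as mean ± standard deviation (SD"). The section expects Bayley-III scores to be normally distributed and makes no such statement about UIC.

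**The concern.** Medians and a percentage increase are the usual way to plan for a right-skewed concentration. An ANCOVA of UIC as measured, linear in baseline UIC as measured, gives a difference in arithmetic means. If UIC is skewed, the reported effect cannot be set directly against the planned 120 versus 80. For example, if UIC is lognormal with log-SD 0.616 and the medians are 80 and 120, the mean difference is 40 × exp(0.616²/2) = 48.4 μg/L, not 40.

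Two further things are at stake. If the effect is proportional, the spread is larger in the cod arm, and the raw-scale model can lose power. Enrolment closed at 137 against the 144 planned, so women cannot be added, and the choice of scale is one of the few levers left. Also, while the scale is only implied, it could be chosen after the data have been seen.

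**Working it through.** **1. The plan's own power figure.** It cannot be reproduced, because no SD is stated. It can be inverted. With n = 60 per arm, two-sided α = 0.05 (sidedness is not stated, so this is assumed) and 95% power:

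SD = δ × √(n/2) / (1.960 + 1.645) = δ × 5.477 / 3.605

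| Planned effect | δ | Implied SD |
|---|---|---|
| Ratio 1.30 (30% higher) | ln 1.3 = 0.262 | log-SD 0.399 |
| Ratio 120/80 = 1.50 | ln 1.5 = 0.405 | log-SD 0.616 |
| 80 to 104 (30% higher), raw | 24 μg/L | 36.5 μg/L |
| 80 to 120, raw | 40 μg/L | 60.8 μg/L |

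Two log-SDs are implied because the document gives two effects: 30% above 80 is 104, whereas 120 is 50% above 80. Each log-SD belongs only with its own ratio.

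**2. Is skew plausible on the documents' own figures?** Only indirect evidence exists.
- A normal variable centred at 80 with SD 60.8 would be negative with probability Φ(−80/60.8) = 9%. With SD 36.5 the figure is 1.4%.
- The Background gives a median iodine intake of 166 μg/day with supplements (141 from food alone), with 21.7% reaching 250 μg/day. The normal quantile for 21.7% above is 0.782. A normal distribution would need SD (250 − 166)/0.782 = 107, or (250 − 141)/0.782 = 139, putting 6% or 16% of intakes below zero. A lognormal distribution needs log-SD ln(250/166)/0.782 = 0.52, or ln(250/141)/0.782 = 0.73.

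These intake figures come from another cohort and are not UIC, so they make right skew plausible but do not establish it.

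**3. Power of the two scales if UIC is lognormal.** Simulation with control median 80, two-sided 0.05, and 55 per arm (137 × 0.8 = 109.6 women after the plan's 20% dropout). The pre-post correlation is not in the document and is assumed to be 0.3 to 0.5.

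| Ratio, implied log-SD | Raw ANCOVA | Log ANCOVA |
|---|---|---|
| 1.3, 0.399 | 92.4–96.3% | 94.3–97.7% |
| 1.5, 0.616 | 89.6–93.5% | 94.8–97.5% |

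Type I error is about 5% on both scales. At 60 per arm, ratio 1.5, log-SD 0.616 and correlation 0.3, log ANCOVA reaches about 96%; raw ANCOVA needs about 70 to 75 per arm to match it.

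At a larger spread than the plan implies (log-SD 0.8, 60 per arm), ratio 1.5 gives 69–75% raw and 82–88% log; ratio 1.3 gives 35–40% raw and 46–54% log.

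**4. An additive shift.** The fixed 400 μg/week rationale might suggest one. At +24 μg/L, log-SD 0.4 and 60 per arm, power is 95.8–98.1% raw and 99.3–99.8% log. With gamma-shaped UIC (CV 0.6, 55 per arm) it is 69% raw and 88% log.

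**5. Where the gain reverses.**

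| Shape and effect | Raw | Log |
|---|---|---|
| Gamma, CV 0.5, ratio 1.3, 55 per arm | 83% | 79% |
| Gamma, CV 0.6, ratio 1.3, 55 per arm | 67% | 61% |
| Gamma, CV 0.7, ratio 1.5, 55 per arm | 89% | 82% |
| Normal, SD 30–36.5, +24 μg/L, 60 per arm | 96.0–99.9% | 92.6–99.6% |
| Normal, SD 30–36.5, ratio 1.3, 60 per arm | 91–99% | 60–89% |

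The gamma rows use correlation 0.4 and the normal rows 0.3 to 0.5. The last row is the most adverse case for the log scale. Its size depends on a few near-zero values, floored at 5 μg/L in the simulation, which become extreme after taking logs.

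**The case against.** - **The scale is not stated.** A reader might infer that the protocol prescribes untransformed UIC and rules out logs. It does neither. The mean and SD sentence covers all continuous variables and concerns summaries, and an analysis plan that is not shown could add a transformation. That stands. But the article does name the model, outcome and covariate, all as plain UIC, so the ordinary reading is the raw scale, and that does not match the planned effect.
- **Log is not always the more powerful scale.** A reader might infer that skew plus a relative effect guarantees a gain. The gamma results above refute this: the data are right-skewed, the effect is proportional, and raw wins by 4 to 7 points. The primary sample also pools spot urine from six consecutive days, which dampens within-woman extremes, so the document does not show that a few very high values would dominate the estimate. This stands and makes the gain conditional.
- **Large gains at ratio 1.3 mix inputs.** Applying log-SD 0.61 to ratio 1.3 gives gaps of roughly 8 to 10 points, but that spread is implied by ratio 1.5. With the matching 0.40 the gain is 1 to 2 points. This stands.
- **The planned quantity is not unique.** The document gives both 30% and 50%, and its intake rationale is a mean with a fixed addition. This stands in part: the UIC target itself is stated as a percentage and as medians, and both forms are ratios.
- **The raw analysis is valid.** Its type I error is near nominal in the simulations. This stands; the issue is alignment and efficiency, not validity.

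**Conclusion.** The concern holds as a mismatch between planning and analysis: the effect is planned as a ratio of medians, and the primary model as worded yields a difference in means. It is a reason to fix the scale in advance, not evidence that the raw analysis would mislead.

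Under lognormal UIC, 55 per arm and a pre-post correlation of 0.3 to 0.5, the log scale adds about 1 to 2 points of power (ratio 1.3) or 4 to 5 points (ratio 1.5) at the spreads implied by the plan's own 95%. It adds more with greater spread or an additive shift. With a purely proportional effect it loses several points if UIC is gamma-shaped, and can lose more if UIC is close to normal. The documents give no SD or shape with which to choose among these cases.

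It would be wrong to infer that the log analysis is more powerful in every case or free of cost. The effect measure changes, and the ratio of geometric means equals the ratio of medians only if log UIC is symmetric. The case for logs therefore rests first on matching the planned effect, and only conditionally on power.

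**What to change.** Before unblinded analysis, state in the protocol or analysis plan:

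1. Primary analysis: ANCOVA of log(post-intervention UIC) on arm and log(pre-intervention UIC).
2. Effect measure: ratio of geometric means, cod versus control, with 95% CI.
3. Descriptive summary of UIC: median and interquartile range, in place of mean and SD.
4. Sensitivity analysis: raw-scale ANCOVA with robust standard errors, giving the difference in μg/L.

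Separately, reconcile the 30% increase with the 120 versus 80 medians, so that the estimated ratio has one planning value to be read against.

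The cost is a few sentences and no new data. The primary effect is then read as a ratio, with the μg/L difference still available from the sensitivity analysis, and some power is given up if UIC proves close to normal or gamma-shaped with a proportional effect.

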**Method:**

Two-armed randomized trial where 137 pregnant women were randomized to either receiving cod twice weekly, or continue with habitual diet for 16 weeks (pregnancy week 20–36). Socioeconomic- and demographic factors, dietary information and biological (urine, blood, and hair) samples are collected pre- and post-intervention, and at six weeks, three-, six-, and eleven months postpartum. Biological samples (urine, blood, and hair) of the infant are collected at six weeks, three-, six-, and eleven months postnatal. Child development is assessed by The Bayley Scale of Infant and Toddler Development, 3rd edition, at eleven months, and by parent report on the Ages and Stages Questionnaire, 3rd edition, and Ages and Stages Questionnaire: Social Emotional at three-, six-, and eleven months.

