**Fig. 1 Fig1:**
[figure not shown]
Overview of study schedule and main activities. *Six consecutive days between GW 18 and GW 19 and between GW 35 and GW 36 (last days of intervention meal). †Questionnaire includes: participant characteristics; self-reported maternal mental health; and parent-reported infant mental health. Abbreviations: GW, gestational week; M, mother; I, infant; U, urine; S, serum; T4, thyroxine; T3, triiodothyronine; RBC, red blood cells; FA, fatty acids; H, hair; FFQ, Food Frequency Questionnaire; ASQ-3, The Ages and Stages Questionnaire; ASQ:SE, The Ages and Stages Questionnaire: Social Emotional; BISQ, Brief Infant Sleep Questionnaire; EPDS, The Edinburgh Postnatal Depression Scale; HADS, The Hospital Anxiety and Depression Scale. ^‡^Screening tool for eating disorders

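### The Bayley-III model fixes no prognostic covariate and adds covariates only after group differences are seen, so it gives up some precision on aim (2) that fixed adjustment could recover

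*Protocol article*

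**What the plan says.** All of the modelling text is in the protocol article, Statistical considerations, Data analysis.

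- **Primary outcome.** Post-intervention UIC is analysed by ANCOVA "with the pre-intervention UIC as a covariate". The reason given is that the later value is expected to depend partly on the earlier one.
- **Secondary outcome.** "For the secondary outcome, we will use linear regression to compare the mean Bayley-III cognitive score", together with the language scores (receptive, expressive, composite) and the motor scores (fine, gross, composite), between the two groups. That makes seven scores. No covariate is named.
- **Adjustment.** "In the case of unanticipated differences occurring between the intervention and control group", the plan says, "we will adjust for that/those factor(s) in the analyses for both the primary and secondary outcome".
- **Exploration.** "We will also investigate potential effect modification by other nutrients and confounding factors".

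Elsewhere, the Trial design section states that "the secondary outcome is neurodevelopment assessed by the cognitive, language and motor scales" of the Bayley-III at 11 months. On data available before the intervention, the abstract says: "Socioeconomic- and demographic factors, dietary information and biological (urine, blood, and hair) samples are collected pre- and post-intervention". The legend to Fig. 1 adds: "Questionnaire includes: participant characteristics; self-reported maternal mental health" and parent-reported infant mental health.

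**The concern.** The plan adjusts the primary outcome for a variable because that variable predicts the outcome. It does not carry this reasoning over to Bayley-III. An infant has no pre-intervention Bayley score, so any gain in precision has to come from other variables, and none is fixed.

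The conditional rule does not fill the gap, because it answers a different question. It reacts to chance imbalance, whereas precision adjustment removes outcome variance. If the arms are balanced, the rule adds nothing, however prognostic a factor is. If they are not, a factor enters because it differs between arms and not because it predicts development.

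Infant development is one of the trial's two stated aims. The sample size calculation concerns UIC only, and enrolment has closed at 137 women. Apart from limiting further drop-out, precision on this aim can now come only from the analysis.

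**Working it through.** **1. What the text fixes.** Three statements stand side by side: a named covariate for UIC; a comparison of means between groups, with no covariate, for Bayley-III; and adjustment conditional on differences seen. A rule for adding factors under a condition implies a base model without them. That is an inference, since the section never says that study group is the only term.

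**2. No figure of the plan's own to reproduce.** The article gives no SD, target difference, power or covariate R2 for Bayley-III. The calculation is therefore in SD units, with R2 as an assumption.

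**3. Inputs.**
- Enrolled: 137 (Trial status). Drop-out: 20% (Sample size calculation). 137 × 0.80 = 109.6, or about 55 per group. Equal arms are assumed.
- Significance level: 0.05 (Data analysis). Two-sided is assumed, as the article does not say.
- Number of covariate terms: k = 2 (assumed).
- R2: 5%, 10% or 20% (assumed).

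**4. Unadjusted comparison.** A two-sample t-test (noncentral t, 108 df, 55 per group) detects 0.539 SD with 80% power. Power for 0.5 SD is 74%.

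**5. Effect of adjustment.** The variance of the group difference is multiplied by (1 − R2) and by a cost factor for estimating the covariates. With N = 110:

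cost = 1 + k/(N − k − 3) = 1 + 2/105 = 1.019

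SE ratio = √[(1 − R2) × 1.019]

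| Assumed R2 | SE ratio | 80%-power difference | Power for 0.5 SD |
|---|---|---|---|
| Unadjusted | 1.000 | 0.539 SD | 74% |
| 5% | √(0.95 × 1.019) = 0.984 | 0.530 SD | 75% |
| 10% | √(0.90 × 1.019) = 0.958 | 0.516 SD | 77% |
| 20% | √(0.80 × 1.019) = 0.903 | 0.487 SD | 82% |

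**6. Break-even.** (1 − R2) × 1.019 = 1 gives R2 = 1.9%. Below that, two covariates cost slightly more than they return. In the worst case, R2 = 0, the SE rises by √1.019 − 1 = 0.9%, the detectable difference becomes 0.544 SD and power for 0.5 SD is 73%.

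**7. More terms cost more.** With five terms the same factor is 1 + 5/102 = 1.049, so an R2 of about 5% would bring no net gain. The set has to be small.

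**The case against.** The strongest objection is that a covariate list for a secondary outcome is usually left to the analysis plan or full protocol. Neither is shown, and a journal article condenses them. The absence of a list is therefore not in itself a fault. This stands, and the point does not rest on it. It rests on what the section does state: a covariate where one is intended, and a rule that makes further adjustment conditional on observed differences. If an unseen plan already fixes Bayley-III covariates, the point falls.

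A reader might draw four stronger conclusions that the document does not support.

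- **That Bayley-III is definitely regressed on study group alone.** The article does not say so. Linear regression can carry covariates, and the adjustment rule explicitly covers the secondary outcome.
- **That the planned test is biased or has the wrong error rate for want of covariates.** In a randomised comparison, leaving out prognostic factors costs efficiency only.
- **That maternal education and infant sex are on file.** Neither is named. The text speaks of socioeconomic and demographic factors and of participant characteristics. Both variables are plausible, but their availability is an inference.
- **That these would be the only variables available for precision.** Pre-intervention UIC, thyroid hormones, iron status, diet and maternal mental health are also collected.

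It is also fair to say that the gain is modest. At an R2 of 5% the SE falls by only 1.6%.

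**Conclusion.** The point holds as a low-cost improvement, not as an error that undermines the analysis. As written, the plan fixes no prognostic covariate for Bayley-III and ties adjustment to observed imbalance. It can therefore forgo precision when the arms are balanced, and choose covariates on the wrong criterion when they are not.

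The SE would fall by about 1.6%, 4.2% or 9.7% at an assumed R2 of 5%, 10% or 20%. That is negligible at the bottom of the range and useful at the top. These figures assume 55 infants per group, two covariates and a two-sided 5% test. R2 is the decisive input, and the document gives no means of estimating it.

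**What to change.** In Data analysis, or in the analysis plan if one exists, state that:

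- each Bayley-III score is regressed on study group plus a small, named set of covariates chosen for expected prognostic value;
- the set comes from the pre-intervention socioeconomic and demographic data (for example maternal education, if recorded) and infant sex (if recorded), which a diet begun at about week 20 cannot change;
- the set is fixed before the 11-month data are analysed by arm and applied whether or not the arms differ;
- the unadjusted difference is reported as a sensitivity analysis.

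This adjusted model would take the place of imbalance-triggered adjustment in the main Bayley-III analysis.

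The cost is one sentence, with no new data, visits or participants. Two terms use two of 108 residual degrees of freedom, and the SE rises by about 0.9% if the covariates prove to have no prognostic value. The article is dated 17 January 2018 and gives September 2018 for completion of the 11-month follow-up, so at issue there was still time to fix the set before any analysis by arm.
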